### Recruitment and consent

2.4.

As part of routine care at the participating obstetrics clinics, any patient who believes they may be pregnant undergoes a pregnancy test and an ultrasound for confirmation of pregnancy followed by a nurse intake visit if a viable pregnancy is identified. The nurse intake visit is ideally performed at 8 weeks gestation. Patients then return 1–2 weeks later to meet the obstetrician or advance practice provider for an initial prenatal visit and begin prenatal care. During the initial 8-week nurse visit, all patients are screened for FI using the validated 2-item Hunger Vital Sign^™^ [35]. The measure asks: 1) “Within the past 12 months you were worried that your food would run out before you got money to buy more”, and 2) “Within the past 12 months the food you bought just didn’t last and you didn’t have money to get more.” Participants who respond “Often true” or “Sometimes true” to either question are considered food insecure, and responses to the items are captured as structured data elements in the electronic health record (EHR). Compared to the USDA FSSM (gold standard for assessing food security) [7], this 2-item measure has high sensitivity (97 %) and good specificity (83 %) and has been used in numerous prior studies in clinical settings [35–38]. Given this is a pilot study with a small sample size and to allow the interventions time to take effect, we will only include patients who are presenting in their first trimester (exclude patients presenting for the initial nurse visit in their 2nd or 3rd trimester). Using structured EHR data and a recurring weekly query, our research team will call all patients who are potentially eligible prior to their initial visit with the obstetrician/midwife to introduce them to the study and determine interest in participating. Potentially eligible and interested patients will be approached in the clinic at the time of their visit to assess eligibility, discuss study procedures, obtain consent, and collect baseline data. Patients will be eligible if they meet the prespecified inclusion and exclusion criteria (Table 1). After baseline data are obtained, participants will be randomized. We will continue this process until we reach our target sample size of 60 (see Power and Sample Size).

### Interventions

2.5.

As part of usual care, all participants in the study will receive routine prenatal care from their regular obstetrics team. Though FI often goes untreated in clinical care, not offering assistance for FI in a research setting poses unacceptably high risks to participants. We therefore propose a comparative effectiveness design, initially comparing HER-based WIC referral to WIC referral + care navigation. As both strategies are plausibly beneficial, but neither is known to be efficacious for improving FI or maternal-child health nor superior to the other, the principles of clinical equipoise are met.

#### Stage 1 interventions

2.5.1.

EHR WIC referral: Participants randomized to this intervention will be referred to the WIC program through an already developed electronic referral process [39,40]. The process securely sends a referral to WIC program staff via the EHR. To enable WIC offices to electronically receive referrals and communicate with healthcare teams, our EHR offers a community provider-facing, read-only version which WIC staff have been certified and trained to use under an existing memorandum of understanding between AHWFB and county health departments.EHR WIC referral + care navigation: Participants will receive the same intervention as above. In addition, a bilingual patient care navigator will meet with the participant at enrollment to discuss any barriers to accessing WIC. The purpose of the visit is to build rapport and trust and to identify any social or structural barriers to enrolling in WIC. The navigator will also contact participants at 2 weeks to discuss any additional barriers reported and as necessary after the baseline visit. Specific counseling will be tailored based on individual’s needs (i.e., difficulty with paperwork). The navigator will also assess any additional community resources available to assist the participant (e.g., food pantries). All encounters between the navigator and participant will be documented and reviewed by the study team to assess fidelity.

#### Suboptimal improvement

2.5.2.

We will re-assess all participants at 3 months using the 10-item FSSM. Participants who do not have a ≥ 2-point decrease in FI, whether they enrolled in WIC or not, will be re-randomized to 1 of 2 second-stage interventions. We selected a decrease of 2 points and time horizon of 3 months based on prior studies, which have shown that receipt of government benefits (WIC, Supplemental Nutrition Assistance Program (SNAP)) results in approximately a 2-point decrease in FI over that time period [22,23,41]. Although studies have shown that interventions to address FI during pregnancy improve food security, prior studies have not quantified the amount of change in FI and differences in pregnancy outcomes. Previous studies have shown a 2-point decrease in FI is associated with clinically meaningful improvements in quality of life and mental health [42].

#### Stage 2 interventions

2.5.3.

Produce Rx: Participants randomized to this arm will receive $10 worth of fruits and vegetables each week from our community partner, Help Our People Eat (H.O.P.E.) of Winston Salem. H.O.P.E. is a non-profit that distributes nutritious meals and fruits and vegetables to neighborhoods throughout Forsyth County to help families with FI. H.O.P.E. also collaborates with local farmers to provide a Neighborhood Produce Market that provides low-cost produce. Through H.O.P.E’s prior work, $10 of produce provides enough fruits and vegetables for a family of 4 for 2–3 days. Weekly deliveries of produce will be made to a participant’s home for 3 months, include a mix of fruits and vegetables depending on the season, and provided by local farmers.MTM: MTM will be provided by our community partner, Providence Kitchen, a program of Second Harvest Food Bank of Northwest NC. Participants will receive 10 medically-tailored refrigerated or frozen meals (5 lunches and 5 dinners) delivered to their home weekly for 3 months. All meals are planned by a registered dietician and tailored to meet the nutritional needs of pregnant women. Meals will require minimal preparation time, and will be packaged such that they can be re-heated by stove, oven, or microwave. Participants will be asked not to share the meals with family members. Consumption of meals and food sharing with other household members will be measured using food consumption diaries.

### Outcomes

2.6.

We will assess outcomes based on the impact of FI on health and RE-AIM conceptual frameworks [31–33,43–46]. We will focus on 3 parts of RE-AIM (Reach, Effectiveness, and Implementation). “Reach” refers to the proportion of the target population who participate, “Effectiveness” to the impact on the desired outcome, and “Implementation” to the fidelity with which the designed intervention is carried out. Our primary outcome in Aim 1 is the feasibility of recruitment or reach, i.e., the proportion of eligible, approached patients who enroll in the study. Our primary outcome in Aim 2 is the feasibility of retention, i.e., the proportion of eligible participants who complete 3-month and 6-month follow-up data. We will also assess the feasibility of re-randomization, i.e., the proportion of eligible participants in Stage 1 who are re-randomized to a stage 2 intervention. To assess potential effectiveness, we will utilize the 10-item USDA FSSM [7]. The FSSM was developed using a Rasch model, which supports an interval interpretation of the raw score and can be evaluated as a continuous or binary outcome (food secure vs food insecure) [7]. We will assess FI as a continuous outcome in our primary analysis and as a binary outcome in secondary analyses. We will conduct process evaluation to document intervention delivery and fidelity. We will assess how many participants enrolled in WIC, how often participants met with the WIC provider, how often participants received the Produce Rx, the number of MTM delivered, and adherence to the MTM. The navigator will also maintain a log of their interactions with participants, including the mode of delivery (phone, in-person), time spent, and what was discussed. We plan to evaluate additional secondary or exploratory outcomes as included in Table 2.

### Data collection

2.7.

We will administer surveys at baseline (prior to randomization), 3 months (prior to re-randomization), and 6 months. To minimize participant burden, follow-up assessments will be conducted by phone and participants will be sent the survey by email ahead of the call. Participants will be called up to 5 times at each time point at which measures are collected. Because all participants will be patients at AHWFB, we will also be able to follow-up with participants at their prenatal care visits if we are unable to reach them by phone. We will provide graduated compensation ($20 at baseline, $40 at 3 months, and $60 at 6 months) to reduce the risk of loss to follow up. Surveys will be collected using REDCap, a secure application for building and managing surveys and databases. Participants will complete the surveys on a tablet or computer at their baseline visit and over the phone at follow-up visits. We will also extract data from the EHR regarding participants’ demographics, clinical characteristics, and outcomes (Table 2). Study staff will place CGM devices on participants at the initial in-person baseline visit and mail them to participants at 6 months to self-place. Participants will receive video and written instructions on the CGMs. After 14 days, staff will instruct participants on device removal. The device is painless to apply, requires no interaction after placement, and should not hinder activities of daily life. The device results will be blinded to avoid participants changing behavior based on the readings.

As quantitative measures may not fully capture the complex behavioral and contextual processes, an embedded qualitative approach has been included to produce a richer understanding of the interventions’ effects. We will conduct semi-structured interviews (in English or Spanish) with 2 groups of participants at the end of their 6-month follow-up: participants who 1) had a ≥ 2-point decrease in FI (*n* = 15) and 2) did not have ≥2-point decrease in FI (n = 15). The sample size of 30 participants should be adequate to reach thematic saturation, but we will have flexibility to expand if warranted. Interviews will help generate hypotheses about potential mechanisms of intervention effects, inform future modifications, assess acceptability of the interventions, and help further develop an effective adaptive intervention. Those who complete an interview will receive an additional $25.

### Power and sample size

2.8.

As this is a pilot study, it is primarily designed to determine the feasibility of recruitment, re-randomization, retention, data collection, and adaptively providing FI interventions. Data from this study will provide critical information to refine the study protocol and estimate measures of variance to assist in sample size calculations to inform a future fully-powered SMART. To justify our plan to enroll a target number of study participants in this study, we will follow a confidence interval-based approach [47,48]. Compliance, defined as *p* = 0.9, will be used as the primary outcome in this calculation. We aim to recruit a sufficient number of participants, n, to obtain a margin of error of 0.075 around estimated compliance with 95 % confidence. To conservatively account for up to 25 % attrition, we aim to recruit for a final enrollment of *n* = 60. A sample size of 60 also provides a minimum probability of 80 % of observing at least 5 participants in each subgroup assuming a 40 % response rate for the Stage 1 interventions and 25 % attrition across the entire study period [49,50]. To calculate the power and sample size for a fully-powered trial, both the potential effect size and Stage 1 intervention response rate (proportion of participants who are re-randomized) are necessary for a SMART design. As this is the first study to test an adaptive food insecurity intervention among pregnant individuals, results from this pilot will provide critical information to plan the future trial.

### Statistical analysis

2.9.

In accordance with intention-to-treat, all 60 participants randomized in stage 1 will be included in all analyses. We will summarize participant characteristics at baseline using means and standard deviations (or medians and interquartile ranges) for continuous variables and frequencies and percentages for discrete variables. We will summarize the distribution of FI and secondary outcomes at baseline, 3 months, and 6 months. Our approach to handling incomplete or missing data will depend on the causes and amount. We will determine the likely reasons for missing data (ignorable or not ignorable) and use appropriate methods to address those reasons (e.g., multiple imputation for ignorable). We will use a time-ordered conditional imputation strategy specifically designed for SMART data if we perform multiple imputation [51].

For Aim 1, we will use descriptive statistics to summarize the feasibility (proportion of eligible patients who enrolled). We will also assess the change in FI, dietary intake, food expenditures, psychological outcomes, and healthcare use based on survey responses and EHR data extraction at baseline and 3 months. Given our small sample size, we do not expect to see significant differences in outcomes between participants who were randomized to WIC referral versus those randomized to WIC referral + navigation. Although not the goal or expected, a sample size of 60 does provide sufficient power (0.9) to detect a 2-point difference (SD: 2.0) between the 2 arms with an alpha of 5 % and assuming up to a 25 % loss to follow-up (22 participants per group) using a two-sample *t*-test.

For Aim 2, participants who have a suboptimal improvement in FI (<2-point) at 3 months will be re-randomized in stage 2 resulting in four embedded adaptive interventions (Table 3). To evaluate change in outcomes over time across the four adaptive interventions in the SMART design, piecewise (segmented) marginal mean regression models (fit using generalized estimating equations (GEE)) will be used [52]. In this pilot study, we do not expect to see significant differences between interventions given our small sample size. We will use descriptive statistics and two-stage piecewise GEE regression models to assess differences in outcomes. The fit of this model to our data will inform estimates of variance and the correlation matrix that are necessary to conduct piecewise regression models to assess the differences in a future, fully-powered SMART.

For Aim 3, the semi-structured interviews will occur via telephone and be digitally recorded and transcribed (and translated), with identifying data removed, and guided by a semi-structured interview guide. The guide will be based on the RE-AIM framework. Analyses will be conducted by 2 trained staff, working in parallel, guided by the constant comparison method, and informed by grounded theory methodologies [53–56]. This approach is well suited for systematically uncovering participant experiences and comparing them within and across groups. Analytic steps will include: 1) after each interview, interviewers will document field notes; 2) transcripts and field notes will be entered into Atlas.ti software (Berlin, Germany) for coding and analysis; 3) we will develop a preliminary codebook to include pre-determined deductive codes and inductive codes that emerge from the data; 4) coding differences will be discussed and negotiated until consensus is reached and high inter-rater reliability (k ≥ 0.80) is achieved; 5) similarities and differences will be examined and themes developed; 6) we will “member check” themes to refine and establish the validity of the results. From these rich data, we will gain a greater understanding of how and why interventions produced the outcomes they did and develop a conceptual understanding of how interventions to address FI can most effectively improve care for pregnant patients.

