### Overall study design

2.3.

Guided by the impact of FI on health and Food is Medicine conceptual frameworks [17,31–33], the objectives of the “Feasibility of an ADAPTive intervention to improve food security and Maternal-Child Health (ADAPT-MCH)” are to: 1) determine the feasibility of recruitment and retention and 2) generate preliminary estimates of the potential effectiveness of the interventions in anticipation of a large, definitive SMART to improve FI. A fully-powered SMART is needed to answer two questions: 1) as WIC is an evidence-based program shown to reduce FI and improve pregnancy outcomes, is a direct electronic health record (EHR) referral to WIC enough to reduce FI or do pregnant patients not already enrolled in WIC need a referral plus assistance from a care navigator? 2) for people who do not have an improvement in FI from the initial intervention, should healthcare settings provide Produce Rx or MTM? This pilot study is necessary to determine the feasibility of recruitment, re-randomization, retention, data collection, and adaptively providing FI interventions [34]. Data from this study will provide information to refine the study protocol and estimate measures of variance to assist in sample size calculations to inform a future fully-powered SMART.

The proposed pilot study is a single site two-stage SMART (Fig. 1). We will enroll 60 patients who are pregnant and food-insecure from obstetrics clinics affiliated with AHWFB. Using a computer-generated randomization table to ensure allocation concealment, eligible consenting participants will be equally randomized using permuted blocks of size 2,4, or 6 (1:1) to 1 of 2 first-stage interventions: 1) EHR referral to WIC or 2) EHR referral to WIC + care navigation. We will re-assess all participants at 3 months. Participants who do not have ≥2-point decrease in FI based on the 10-item adult USDA Food Security Survey Module (FSSM) (suboptimal improvement, i.e., non-responders) will be equally re-randomized using permuted blocks of size 2, 4, or 6 to 1 of 2 second-stage interventions: 1) Produce Rx or 2) MTM [7]. The USDA FSSM with a 30-day look back period measures food security over the prior 30 days. We will use the standardized scoring provided by the USDA, which produces a raw score from 0 to 10 with higher scores indicating worse FI. Due to the nature of the intervention, neither study staff nor participants are blinded to their assigned group.

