## Figures and Tables

**Fig. 1. F1:**
[figure not shown]
Overall study design. We will conduct a single site pilot sequential multiple assignment randomized trial (SMART). Patients (N = 60) who are pregnant and food insecure will be randomized to receive one of 2 interventions in Stage 1:1) EHR referral to WIG or 2) EHR WIC referral + care navigation. We will follow up all participants at 6 months Participants who do not have ≥2 point decreased in food insecurity at 3 months (suboptimal improvement) will be re-randomized to one of 2 interventions in Stage 2: 1) Produce Rx or 2) MTM. We will follow up all participants at 6 months. EHR-electronic health record; MTM-medically tailored meals; Produce Rx-produce prescriptions; WIC-Special Supplemental Nutrition Assistance Program for Women, Infants, and Children.

**Table 1. T1:** Inclusion and exclusion criteria.

Inclusion	Exclusion
1. ≥18 years of age	1. Planning on moving out of the area within 6 months
2. Confirmed viable pregnancy by their obstetrician or midwife based on urine pregnancy test and ultrasound	2. Severe cognitive impairment or major psychiatric illness that prevents consent or serious medical condition which either limits life expectancy or requires active management (e.g., certain cancers)
3. Experience FI based on the 2-item Hunger Vital Sign^™^	3. Lack safe, stable residence or the ability to store the MTM
4. Speaks English or Spanish	4. Lack of a telephone
5. Not currently enrolled in WIC	5. Severe food allergy or require a specialized diet (e.g., Celiac)
6. First trimester at the time of the initial prenatal visit	

**Table 2. T2:** Study outcomes and measures.

Measure	Potential sample measures and citations	Data source	Month
Primary outcomes			
Feasibility of recruitment/proportion recruited (**Aim 1**)	Proportion of eligible patients who enroll	Study logs	0
Feasibility of retention/proportion retained (**Aim 2**)	Proportion of participants who complete follow-up data collection	Study logs	6
Feasibility of re-randomization/proportion rerandomized (**Aim 2**)	Proportion of eligible participants who are re-randomized to stage 2 interventions	Study logs	3
Food insecurity (**Aim 1 and 2**)	10-item USDA FSSM with 30-day reference period [7]	Survey	0, 3, 6
Maternal outcomes			

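### Participants with a baseline FSSM score of 0 or 1 cannot meet the 2-point response rule, so the Stage 1 response rate mixes non-response with inability to respond

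*Protocol article*

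**What the plan says.** **Entry.** Table 1 requires "Experience FI based on the 2-item Hunger Vital Sign". None of its six inclusion criteria refers to the FSSM. Section 2.4 gives the screener items, the first being "Within the past 12 months you were worried that your food would run out before you got money to buy more". Patients who answer often true or sometimes true "to either question are considered food insecure". The same section reports the screener's sensitivity (97%) and specificity (83%) against the FSSM.

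**Response.** Section 2.3 says that "The USDA FSSM with a 30-day look back period measures food security over the prior 30 days" and that its scoring "produces a raw score from 0 to 10 with higher scores indicating worse FI". Response is a fall of at least 2 points at 3 months. Section 2.5.2 sends everyone else on: "whether they enrolled in WIC or not, will be re-randomized to 1 of 2 second-stage interventions". Section 2.9 repeats it for Aim 2: "participants who have a suboptimal improvement in FI (<2-point) at 3 months will be re-randomized in stage 2". No section makes an exception for a low starting score or for being food secure at 3 months.

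**Use of the result.** Section 2.8 assumes a 40% Stage 1 response rate and 25% attrition. From these it derives a probability of at least 80% of seeing 5 or more participants in each subgroup. It also calls the Stage 1 response rate necessary for sizing the full SMART. The FSSM is collected at baseline before randomisation (Section 2.7, Table 2).

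**The concern.** Entry and response use different instruments with different look-back periods. One positive answer about the past year admits a patient whose score for the last 30 days may be 0 or 1. Such a patient is a non-responder by construction, whatever the WIC referral or the navigator achieves.

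Two things are at stake:

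- **The response rate.** It is one of the main figures the pilot is to hand on, and it would not separate people for whom Stage 1 failed from people who could not register a success.
- **The re-randomised group.** It would include some people with little food insecurity left to reduce, namely those who are low at 3 months as well as at baseline. This sits awkwardly with the Discussion's rationale that an adaptive approach avoids giving more than a participant needs.

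**Working it through.** **Inputs.** Sample size 60, response 40% and attrition 25% (Section 2.8); 22 completers per arm (Section 2.9); sensitivity 0.97 and specificity 0.83 (Section 2.4); food insecurity in up to 30% of pregnancies (Background). The share *f* of participants with baseline FSSM 0 or 1 is not in the document and is treated as an assumption.

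**1. The plan's own subgroup figure.** Take 22 completers per arm and responders R ~ Binomial(22, 0.4), with non-responders split evenly by blocked re-randomisation. At least 5 are required in each of six cells: responders, Produce Rx and MTM in each arm. The two non-responder cells both reach 5 when 22 − R is at least 10, that is R ≤ 12. So

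P = [Pr(5 ≤ R ≤ 12)]² = 0.918² = 0.843,

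which agrees with the stated minimum of 80%.

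**2. The floor.** The score cannot go below 0, so the largest possible fall equals the baseline score: 0 points from a baseline of 0, and 1 point from a baseline of 1. Both are below 2, so the probability of response is 0, even with a 3-month score of 0.

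**3. Are low baseline scores likely?** The share of screen-positives who are not food insecure on the FSSM, at 30% prevalence, is

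0.17 × 0.70 / (0.97 × 0.30 + 0.17 × 0.70) = 0.119 / 0.410 = 0.29, about 17 of 60.

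This is not the share scoring 0 or 1, because the article states no FSSM cut-off for food secure. It does show that low baseline scores are to be expected.

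**4. Effect for assumed values of *f*.** If the 40% applies only to those able to respond, then:

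- observed response = 0.4(1 − f);
- expected non-responders = 60 × [1 − 0.4(1 − f)];
- share of non-responders at the floor = f / [1 − 0.4(1 − f)].

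The last column repeats step 1 with the reduced response rate. Counts are before attrition.

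| f (assumed) | Observed response | Non-responders of 60 | At the floor | Share at the floor | P(≥5 in all six cells) |
|---|---|---|---|---|---|
| 0 | 40% | 36.0 | 0 | 0% | 0.843 |
| 10% | 36% | 38.4 | 6 | 16% | 0.842 |
| 15% | 34% | 39.6 | 9 | 23% | 0.811 |
| 20% | 32% | 40.8 | 12 | 29% | 0.760 |
| 30% | 28% | 43.2 | 18 | 42% | 0.605 |

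**5. Sensitivity of the last column.** With 23 completers per arm the probability is 0.895 at f = 0, 0.809 at f = 20% and 0.662 at f = 30%, so the point at which it drops below 80% moves a little. If instead 25% are lost at random after an even split, the probability is only about 0.66 at f = 0, so that reading does not reproduce the plan's figure.

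**The case against.** The strongest reply is that this is a feasibility pilot. It expects no significant differences, and its recruitment and retention outcomes do not depend on the FSSM floor. That stands, and it limits the severity.

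Four stronger readings are tempting, and the document does not support them.

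- **That floor participants cannot benefit in Stage 2.** The floor concerns the baseline score. Someone at 0 or 1 at baseline may score higher at 3 months and then has room to improve. The piecewise models of Section 2.9 follow change over time, with the FSSM measured at 0, 3 and 6 months. Only those low at both baseline and 3 months lack room. The 23% to 42% counts people who could not meet the Stage 1 rule, not people who cannot gain from Stage 2.
- **That the response rate is simply biased.** For a future trial with the same entry and response rules, the observed proportion is the right input. It misleads when read as how well Stage 1 works, or when carried to a trial with different entry.
- **That more than half of entrants are not food insecure.** Putting the Background's 13.5% into step 3 gives 53%, but that is a prevalence for U.S. households, not for pregnancies.
- **That eligibility must change now, or that the main analysis should drop those at 0 or 1.** Recruitment has begun. A new criterion would change the denominator of the Aim 1 outcome and add screen failures after consent. It would also select on the baseline value of the outcome, which invites regression to the mean. Dropping randomised participants would contradict the intention-to-treat statement in Section 2.9.

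It is also fair to say that baseline FSSM is collected and will be summarised, so the floor group can be identified afterwards. That is why the remedy is cheap. But nothing in the article says that response will be reported by baseline score.

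**Conclusion.** The structural gap is certain: under the stated entry and response rules, a participant at baseline 0 or 1 is a non-responder and is re-randomised. This follows from the scale and needs no assumption about the data. Both rules are stated in full, so it is not a detail left to another document.

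Its size is unknown, because the article does not give *f*. The range of 15% to 30% is illustrative, and the calculation also assumes that the 40% response applies to those able to respond. On that basis the observed response is 34% to 28%. The subgroup-size statement still holds at f = 15% (0.81), fails at about 20% (0.76) and is about 0.61 at 30%, taking 22 completers per arm and an even split. At f = 10% it is practically unchanged.

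The point is worth correcting because it affects a planning figure the pilot exists to provide. It does not undermine the feasibility outcomes for recruitment and retention.

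**What to change.** - Keep all randomised participants in the intention-to-treat analysis.
- Prespecify that the Stage 1 response rate, the proportion re-randomised and the Stage 2 contrast are also reported by baseline FSSM: 0–1 versus 2 or more.
- For planning the definitive SMART, carry forward two figures together: the response rate among those with baseline 2 or more, and the share at 0–1.
- The sponsor should reconcile the entry criterion with the response and re-randomisation rule for participants at 0–1, and state how they are to be classified. A minimum baseline FSSM score is one option to consider for the definitive trial.

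**Cost.** A short addition to the analysis text and a few more tables, from data already being collected. The split groups will be small and their estimates imprecise, so they should be read descriptively.
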